**C.8.5 Sample size and power**

We will enroll 410 individual women and 410 couples. The combined sample of 1,230 participants will provide 80% power with a type-I error rate of 5% (2-sided) to detect a 10% reduction in the number of unprotected vaginal sex episodes in the repeat HTC arms, net of post-randomization reductions in the control arms. The sample size calculation accounts for within-person and within-couple correlation, estimated at 0.3; a total of 7 assessments, including baseline; 50% cumulative loss to follow-up over 18-months; a control-arm reduction in frequency of 30%; baseline frequency of 5 unprotected episodes per 3 months; and over-dispersion of 2 with respect to a Poisson distribution, used as an approximation to the negative binomial model. To obtain sample size, we modeled the covariance matrix of the parameter estimates in the model used for the primary analysis as the inverse of the sum over participants of matrices X’WX, where X is a matrix of predictor variables specifying time, treatment, and their interaction, with a row for each visit, and W is the inverse of the covariance matrix of the repeated over-dispersed Poisson outcomes, approximated as compound symmetric; for couples, X has two rows per visit. Dropout was accounted for by varying the number of rows of X across participants. This gave an estimate of the SE of the treatment effect estimate, as required in the standard formula for power with a normally-distributed test statistic.

Assumptions above regarding participant retention rate (50%), within-couple correlation (0.3), baseline frequency of unprotected episodes (5 per 3 months), the average reduction in episodes in both arms taken together, and over-dispersion (2), all of which can be estimated without using current information on the treatment effect, will be checked midway through enrolment, i.e. once 50% of the enrolment target has been reached. Power under the planned sample size will then be reviewed using updated estimates for these parameters, under the original assumptions about the treatment effect. If power appears to be low or too high, increasing or decreasing the sample size will be discussed with the study investigators. Because this assessment is made without using current information on the treatment effect, increases or decreases in the sample size can be made with no inflation of the type-I error rate53.54.

In case of persistent difficulties in enrolling couples, we will consider enrolling more single women. Given our assumptions about within-couple correlation, we would only have to enroll 1.7 extra single women for each missing couple. This would weaken inferences about effects in couples, thus would only be considered as a last resort, should couple enrolment fall short of the initial target.

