**Duration**

The qualitative formative phase is planned to last 3 months. The randomized trial phase is planned to last 3 years counting 6-9 months for enrolment and 27-30 months of follow-up. The end-of-follow-up assessment phase is expected to last 6 months

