**Stratified randomized trial**

Participant screening, enrolment & randomization (N=1,230 HIV-negative women)

** Kitgum District Hospital will be only used if trial participant
accrual from St Joseph Hospital is insufficient*

Arm C-2* - Extended repeat HIV retesting and enhanced counselling (ERHTEC)

Couples (N=205 women and 205 men)

Primary outcomes**:

- Rates of unprotected sex, and HIV and STI incidences

- Costs and cost-effectiveness of the intervention

Secondary outcomes**:

- Rates of unintended recurrent pregnancies

- Associations of individual and dyadic variables with primary and secondary outcomes

- Maternal and infant mortality rates

- MTCT of HIV among women acquiring HIV during follow-up

Additional outcomes:

- Acceptability/feasibility, and barriers/facilitators of the intervention

** I-1 = individual control arm / I-2 = individual intervention arm / C-1 = couple control arm / C-2 = couple intervention arm*

*** Both primary and secondary outcomes will be assessed at the end of follow-up, defined as 24 months postpartum or 6 weeks after the end of breastfeeding, whichever occurs first*

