**C. DESIGN AND METHODS**

**C.1 Study Design**

We will conduct a stratified randomized trial of 820 HIV-negative pregnant women and 410 male partners in Mulago Hospital in Kampala and St Joseph District Hospital in Kitgum, Northern Uganda: in each site 205 women enrolled individually and 205 couples will be randomized to be retested and counseled either in late pregnancy (>36 weeks) only as per the WHO/MOH recommendation, or to receive the ERHTEC intervention throughout pregnancy and breastfeeding as follows:

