**C.2.2 Study populations**

Study population for the formative phase: HIV-negative pregnant women and HIV-negative postpartum mothers (FGD 1); partners with any HIV status of HIV-negative pregnant women and HIV-negative post-partum mothers (FGD 2); doctors/clinical officers, nurses/midwives, counselors, and peers (FGD 3). Each FGD will involve 8-10 participants.

Study population for the randomized trial phase: 1,230 HIV-uninfected pregnant women from the Antenatal Clinics (ANC) of Mulago National Referral Hospital in Kampala and St Joseph Hospital/Kitgum District Hospital* in Kitgum, Uganda.

**Kitgum District Hospital will be used only if trial participant accrual from St Joseph Hospital is insufficient.*

Study population for the end of follow-up qualitative assessment: Study staff (health providers, ~10 per site) and women and men trial participants including seroconverted individuals and couples, if any (20 per site).

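### At 50% of enrolment, 18-month retention and the average reduction in episodes cannot yet be estimated, so early values could move the sample size wrongly in either direction

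*Protocol*

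**What the plan says.** Protocol C.8.5 bases the sample size on 50% cumulative loss over 18 months, a 30% control-arm reduction in episodes, a baseline of 5 episodes per 3 months, over-dispersion of 2, correlation of 0.3 and 7 assessments. It then names retention, within-couple correlation, baseline frequency, the average reduction in both arms together and over-dispersion, "all of which can be estimated without using current information on the treatment effect". These "will be checked midway through enrolment, i.e. once 50% of the enrolment target has been reached". If power then looks too low or too high, a larger or smaller sample is to be discussed with the investigators.

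The Protocol Summary (Duration) plans the trial phase as 3 years, "counting 6-9 months for enrolment and 27-30 months of follow-up". Under C.5.1, C.5.2 and the Appendix C summary table, behavioural questionnaires after baseline are given in late pregnancy and at 3, 6, 12, 18 and 24 months postpartum. None is given at the retention visits in between.

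On the target, C.8.5 states "We will enroll 410 individual women and 410 couples. The combined sample of 1,230 participants will provide 80% power", and C.1 describes a "stratified randomized trial of 820 HIV-negative pregnant women and 410 male partners". The Schema has "Participant screening, enrolment & randomization (N=1,230 HIV-negative women" and C.2.2 has "1,230 HIV-uninfected pregnant women from the Antenatal Clinics".

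**The concern.** The check is blind to the treatment effect, which protects the type-I error, but blindness does not make a quantity observable. Retention is defined over 18 months, and the reduction is an average over six follow-up assessments, five of them postpartum. A look taken a few months after the first enrolment sees almost none of that period.

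If early values stand in for these two parameters, the recalculated power answers a different question. The sponsor had raised assumed attrition from 30% to 50% after a comment in grant review (footnote to C.5.4). An early retention figure taken at face value could undo that margin, and a sharp but temporary fall in sexual activity in late pregnancy could prompt an increase that is not needed.

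**Working it through.** **1. The plan's own figure.** Inputs from C.8.5: "80% power with a type-I error rate of 5% (2-sided) to detect a 10% reduction in the number of unprotected vaginal sex episodes"; 410 individual women and 410 couples; 7 assessments; baseline mean 5; follow-up means 5 × 0.70 = 3.5 (control) and 3.5 × 0.90 = 3.15 (intervention); variance = 2 × mean; a single correlation of 0.3 across all rows of a woman or couple. Allocation is 1:1 (Abstract). As C.8.5 describes, the covariance is the inverse of the sum of X'WX, with dropout entered by truncating rows. Loss is taken as linear across visits, which is an assumption.

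- SE of the log rate ratio = 0.0369; |ln 0.90| = 0.1054.
- Power = Φ(0.1054/0.0369 − 1.96) = 81.4%.
- Exponential dropout gives 80.4%; calendar-time dropout with 50% lost by 18 months gives 80.2%.

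The stated 80% reproduces, so the planned sample size is not in question.

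**2. What exists at the look.** Uniform accrual over 6-9 months is an assumption. Half the target is then reached at 3-4.5 months, and mean time since enrolment is 1.5-2.25 months.

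| Visit | Share of those enrolled who are due |
|---|---|
| Late pregnancy | about 8-50% (6-month accrual) or 28-67% (9-month accrual), depending on assumed gestational age at entry |
| 3 months postpartum | 0% (6-month) or 0-9% (9-month) |
| 6, 12, 18 months postpartum | 0% |

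Without the uniform assumption, time since enrolment is still below 9 months, so no 12- or 18-month visit is possible.

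**3. Why high early retention carries little information.** If 50% were lost at a constant rate over 18 months from enrolment, the expected loss at the mean follow-up would be 50% × 1.5/18 = 4.2% to 50% × 2.25/18 = 6.3%. Observed retention of about 95% is therefore what the planning assumption itself predicts at this look.

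**4. Effect on the sample size.** The early values are assumed inputs. Reduction means the control-arm value, as in C.8.5; the pooled quantity that the check would see is (30% + 37%)/2 = 33.5% under the plan.

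- N for 80% power = 1,230 × (2.80 × SE/0.1054)², using the SE at the early inputs.
- True power = Φ(0.1054/(0.0369 × √(1,230/N)) − 1.96), using the planning SE. SEs are unrounded in the calculation.

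| Early retention | Early reduction | Apparent power at 1,230 | N for 80% | True power at that N if 50% and 30% hold |
|---|---|---|---|---|
| 50% (plan) | 30% (plan) | 81.4% | 1,186 | 80% |
| 95% | 30% | 86.4% | 1,032 | 74% |
| 95% | 0% | 89.3% | 942 | 70% |
| 95% | 50% | 81.1% | 1,197 | 80% |
| 95% | 60% | 75.7% | 1,368 | 85% |

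For example, with N = 1,032: 0.0369 × √(1,230/1,032) = 0.0403; 0.1054/0.0403 − 1.96 = 0.65; Φ = 74%. Calendar-time dropout gives 73% and 69% for the second and third rows.

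**5. The target.** 410 + 2 × 410 = 1,230 participants, of whom 410 + 410 = 820 are women. The two labels overstate the number of women by 410.

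**The case against.** Three points in the plan's favour stand.

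- **Three of the five parameters are sound.** Baseline frequency, over-dispersion and same-visit within-couple correlation can be estimated from baseline data.
- **Early data are not empty.** The late-pregnancy visit carries a questionnaire (C.5.1) and retention is monitored monthly (C.5.4). A reader might infer that early data say nothing about later follow-up. That goes too far: they are partial, and reach the planned parameters only by extrapolation.
- **Any change is discussed, not triggered.** C.8.5 sets no automatic rule and does not say that early retention replaces the 18-month figure unadjusted.

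A reader might also infer that the check would shrink the trial. The documents do not support that. The early values are not in the protocol, and the direction is open. The Study concept treats the return to sexual activity after delivery as a critical moment, so a large late-pregnancy fall is as plausible as none, and it points to a larger sample.

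Nor do the wrong labels make the C.8.5 target uncertain, as if the look might come at 615 women. C.8.5 states the composition correctly, the Schema's own arms add up to it, and the power calculation is unaffected.

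**Conclusion.** C.8.5 is wrong in saying that all five assumptions can be estimated at 50% of enrolment. Retention over 18 months and the average reduction over follow-up cannot. That no 12- or 18-month visit can exist follows from the stated 6-9 months of enrolment alone; the scarcity of 3-month questionnaires also rests on roughly uniform accrual.

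The consequence is a risk, not a certainty. Under the illustrative inputs the recalculated sample size runs from 942 to 1,368. True power would then be about 70% at the low end, and about 138 participants would be added without need at the high end (1,368 − 1,230). The claim that a blinded check leaves the type-I error intact is not disputed. The labels of 1,230 women are a real but minor error.

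**What to change.** In C.8.5, limit the look at 50% of enrolment to baseline frequency, over-dispersion and same-visit within-couple correlation. Hold retention (50%) and the control-arm reduction (30%) at their planning values, and state that early retention or early reduction justifies no decrease. A decrease supported by baseline data can stay open: a baseline frequency of 6, for example, gives 88% power and N = 988 with the other planning values unchanged. An increase may still be considered if early loss already exceeds plan.

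The cost is that an early sign of better retention cannot be used to save enrolment. A later check of these two parameters, tied to postpartum visits, is possible but would fall after planned enrolment has closed.

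Separately, correct the Schema and C.2.2 to 820 women and 410 male partners (1,230 participants). State the trigger in the units of C.8.5: 205 individual women and 205 couples, which is 205 + 2 × 205 = 615 participants. All of this is wording; no visit, participant or analysis is added.

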**C.8.6 Qualitative data analysis**

Focus group discussions and in-depth interviews will be transcribed, translated into English, and coded. Analysis will include 3 distinct stages: reducing the data into meaningful segments, naming the segments, combining them into categories or themes and displaying and making comparisons[55](#_ENREF_53) to be used for thematic coding as the primary analytic strategy. After reading 4 transcripts, the analysis team will collaboratively develop a codebook of themes based on interview topics as well as those emerging from the data. Two more transcripts will then be reviewed to include additional topic areas and themes. This process will be repeated until the code-book reaches a stage where no new themes or topic areas emerge. To ensure inter-rater consistency, the analysis team will compare their individual coding of the same transcripts and calculate a coding concordance. All transcripts will then be coded using the final version of the codebook and merged using NVivo software (version 10.0, QSR International, Victoria, Australia). Using NVivo, themes will be summarized across participants. Analysis will focus on identifying dominant explanations for themes identified. Interactive discussions will be held to validate data interpretations and resolve any discrepancies. Our analysis will highlight both, issues described in the study design as well as issues emerging from participant engagement. Trustworthiness will be ensured through the use of different methods for data collection and triangulation of data. A monthly debriefing of the counselors will be held to review counseling notes, triangulating these with relevant quantitative measures

**C.8.7 Data quality and management**

SOPs will be developed for all data management process and procedures to ensure consistency and quality of data. **Quantitative data** will be collected and entered by research staff on CRFs and/or Android electronic tablets (hand-held computers) using “ODK Collect”, a computer-assisted personal interviewing (CAPI) software. The data will be uploaded via internet onto a secure central server according to SOPs. The central web-based server is located in Munich, Germany (http://www.giga-international.com) and is protected by multiple security layers. The data will be stored securely in the central server and backed up into secure central MySQL-server databases at MU-JHU Care in Kampala and at UCSF in San Francisco. These servers are located in access-limited rooms within MU-JHU and UCSF facilities and each computer and each database used to store the data will be protected by separate passwords. Procedures to promote data quality will include skip patterns and range and logical checks built into the ODK Collect entry program, and data validation and cleaning at the point of collection using two levels of quality controls (same-day check and feed-back by data collector and Study Coordinator) according to SOPs.

**Qualitative data** will be collected manually and on a voice recorder and will be transcribed into laptop computers by data clerks and/or research assistants for subsequent coding in NVivo software and analysis. All discussions will be conducted in the local languages, will last no more than 90 minutes, and will be digitally recorded and transcribed into English. Interviewers/research assistants will have experience in qualitative methods including in-depth interviewing and probing where appropriate and relevant. Digital recordings will be transferred to secure computers and deleted from source computers.

All data clerks and managers will have received training on the requirements of strict confidentiality regarding patient identifying information, and laptop security. To protect detailed health and personal information data, study record keeping and access to participant identifying information will follow strict written SOPs and data will be subjected to a variety of quality control procedures. All records will be kept on password protected computers at MU-JHU and UCSF. Participants will be identified primarily by their study number. All CRFs and identifiers will be kept in individual files in secured, access-limited rooms at the sites. Participant names and addresses will be stripped from the database prior to analysis. No individual identifier will be used in any reports or publications resulting from the study. Study investigators and coordinators will continuously mentor and monitor staff to ensure these procedures are followed according to SOPs in order to ensure data quality and confidentiality.

# D. HUMAN SUBJECTS PROTECTION

## D.1 Ethical and regulatory considerations

The study will be conducted in compliance with country specific laws and regulatory requirements. The conduct of the study will also adhere to the GCP principles laid out by the International Conference on Harmonization (ICH) and the Declaration of Helsinki

The protocol and informed consent form will be reviewed and approved by the local IRB in Uganda, UNCST and at UCSF prior to enrollment or carrying out any study procedures. The PI will keep the IRB informed of the progress of the study on a regular basis including any unexpected untoward events, at minimum once a year according to the IRB requirements.

Written informed consent will be obtained from the study participants prior to any protocol-specified procedures being conducted.

To maintain confidentiality, unique study participant identification numbers will be used to identify the subject’s laboratory specimens, source documents, CRF, study reports, etc. All study records will be maintained in a secured location and consents and other identifying information will be kept in a locked cabinet in a room with restricted access which is locked during non business hours.

## D.2 Institutional Review Board (IRB) or Independent Ethics Committee (IEC)

All the documents the IRB/IEC may need to fulfill its responsibilities, such as the protocol, protocol amendments, information concerning subject recruitment, payment or compensation procedures, etc., will be submitted to the IRB/IEC by the investigator. The IRB’s/IEC’s written, unconditional approval of the study protocol and the informed consent form will be in the possession of the investigator/clinical site staff prior to the conduct of any protocol-specified procedures.

Modifications to the protocol will not be implemented without prior written IRB/IEC approval except when necessary to eliminate immediate hazards to the subjects or when the modification involves only logistical or administrative aspects of the study. Such logistical or administrative modifications will be submitted to the IRB/IEC in writing by the investigator, and a copy of the correspondence to verify the submission will be maintained.

The investigator must inform the IRB/IEC of modifications to the informed consent form or any other documents previously submitted for review/approval, of any new information that may adversely affect the safety of the subjects or the conduct of the study, provide an annual update and/or request for re-approval, and advise the IRB/IEC when the study has been completed.

## D.3 Informed Consent

The principles of informed consent will follow ICH-GCP. Informed consent will be documented in writing on a consent form approved by the IRB/IEC in English and translated into the local language.

All relevant information should be provided in both oral and written form in a way that is understandable to the legal guardian of the subject. Ample time and opportunity must be given for the subject to inquire about details of the study. The written consent document will embody the elements of informed consent as described in the Declaration of Helsinki and will also comply with local regulations.

The study counselor will explain the nature of the study, answer study questions and obtain informed consent from the study participants. The original, signed informed consent form for each subject will be maintained by the investigator as part of the subject’s study records. A copy of the signed informed consent form will be offered to each the study participants.

## D.4 Study Completion

The investigator will notify the IRB/IEC when the study has been completed and will provide copies of conference abstracts and publications resulting from the study.

## D.5 Publications and dissemination of study findings

Data analyses and publications will be under the direction of the PI. After briefing the MOH, primary study outcomes will be submitted to the local (SOMREC) and US (UCSF CHR) IRBs for clearance. Once cleared, findings will be presented at a special dissemination workshop involving Kitgum and Kampala stakeholders including the hospitals’ staff, district and MOH leadership, as well as community representatives and non-governmental and community-based organizations. Results will also be summarized in a leaflet written in lay language and translated into Luganda and Luo for distribution to study participants after ethical clearance by SOMREC and UCSF CHR is obtained. Lastly, manuscripts and abstracts will be prepared for submission to national and international scientific meetings as well as peer-reviewed journals.

# E. TIMELINE

|  | **Year 1**  **(2011-12)** | | | **Year 2**  **(2012-13)** | | | | **Year 3**  **(2013-14)** | | | | | **Year 4**  **(2014-15)** | | | | **Year 5**  **(2015-16)** | | | |
| --- | --- | --- | --- | --- | --- | --- | --- | --- | --- | --- | --- | --- | --- | --- | --- | --- | --- | --- | --- | --- |
| Activities Quarter | Q4 | Q1 | Q2 | Q3 | Q4 | Q1 | Q2 | | Q3 | Q4 | Q1 | Q2 | Q3 | Q4 | Q1 | Q2 | Q3 | Q4 | Q1 | Q2 |
| IRB, MOU, planning & CRF design |  |  |  |  |  |  |  | |  |  |  |  |  |  |  |  |  |  |  |  |
| Staff recruitment & site preparations |  |  |  |  |  |  |  | |  |  |  |  |  |  |  |  |  |  |  |  |
| Staff and peer training |  |  |  |  |  |  |  | |  |  |  |  |  |  |  |  |  |  |  |  |
| MULAGO: Screening & enrolment |  |  |  |  |  |  |  | |  |  |  |  |  |  |  |  |  |  |  |  |
| MULAGO: Follow-up |  |  |  |  |  |  |  | |  |  |  |  |  |  |  |  |  |  |  |  |
| KITGUM: Screening & enrolment |  |  |  |  |  |  |  | |  |  |  |  |  |  |  |  |  |  |  |  |
| KITGUM: Follow-up |  |  |  |  |  |  |  | |  |  |  |  |  |  |  |  |  |  |  |  |
| Data cleaning and analysis |  |  |  |  |  |  |  | |  |  |  |  |  |  |  |  |  |  |  |  |

